##### Operational definition of nutritional status

Obese >2 Z of BMI, Overweight >1 Z of BMI, Normal ≥ − 1 y ≤ 1 Z of BMI.

##### Secondary result variable

Percentage of body fat.

##### Optimized physical activity (AFSO) primary dependent variable

Fitness as measured in the lower body by the distance, in centimetres (cm), of a jump done with both feet together and without a run-up, and in the upper body by a dynamometer, which measures the isometric force in kilograms (kg) of the upper body by participants squeezing the instrument with the right and left hand.

#### Healthy Kiosk with nutritional education intervention (KSEAN)

##### Primary dependent variable

Intake of foods measured as consumed and not consumed.

##### Control variable

Physical activity intensity measured using a pedometer during the optimized physical activity classes.

##### Determination of sample size

The sample size was determined as that required to obtain a standard size of the effect of 0.2 on the BMI z-score, based on a previous nutritional and physical education intervention study conducted in primary schools to prevent childhood obesity by Kain et al. in order to identify this effect in four clusters per intervention mode, with a power of 0.8, a significance of 5% and an inter-cluster coefficient of variance of 0.00012 [35], 140 children per cluster are required along with a minimum of 11 clusters, giving a total of 1540 children. Given that this study was conducted in three regions and that each intervention mode must be conducted in each region, a total of 12 clusters and 1680 subjects are required. Assuming a participation loss of 10% in 2 years of intervention, the total sample size would be 1848 children.

It is anticipated that the grip strength dependent variable will be improved by 20% compared to the study conducted by Rojas C et al. [36]. With the sample size calculated in this manner, in order to have a power of 0.8 at a 95% confidence level, 130 subjects per cluster are required, thereby reaching a total of 1560 children between year 1 and year 4.

### Study schedule

The schedule of enrolment, interventions, and assessments is illustrated in Fig. 2. In this figure time point t_1_ corresponds to the time at which the baseline measurements of all variables will be taken and each intervention mode will commence, this time will be aligned with the beginning of the school year. Time point t_2_ corresponds to the first evaluation after commencing each intervention mode, at this time all variables will be measured on every participating child and will be done 8 months later in line with the end of the school year. Time point t_3_ corresponds to the second evaluation, once again all variables will be measured and this time will correspond with the children returning to school from their summer holidays that is 12 months after time point t_1_. Time point t_4_ corresponds to the final evaluation, where once again all variables will be measured. Time point t_4_ corresponds to the end of the second school year of the intervention that is 20 months after time point t_1_. Final result of the study will be delivered to each school and FOSIS 24 months after commencing the interventions at time point t_5_ (Fig. 2).

**Fig. 2 Fig2:**
[figure not shown]
Schedule of enrolment, interventions and assessments

### Recruitment status

To obtain a sample size of 1656 children, a total of 1900 needed to be asked to participate in this study. This is based on an estimate of the proportion of children that would potentially satisfy the inclusion criteria and that would be motivated to participate in this study.

Following a review of the sample strategy and the recruitment of the field personnel, the selection of the potential participants commenced on 8^th^ March 2014. By 25^th^ March 2014 a total of 1923 children had been recruited, exceeding the sample size required.

### Data collection

#### Baseline data collection

During the baseline evaluation, participating children will be interviewed by the field personnel, who have been previously trained for this task. The evaluation is to take place at each participating school, following prior authorization by the relevant municipal authorities and school principals.

The following information will be registered.General information about each participant: name, class, gender, RUT (national ID number), and whether the participant receives benefits under the nutritional school programme and/or the social protection programme. These are government programmes that provide benefits to persons, families or territories that are classed as being in a vulnerable situation [37].Anthropometry: weight, height, skinfolds (biceps, triceps, subscapular, suprailiac).Fitness level: dynamometry of right and left hand to measure the isometric strength of the upper body, and length of jump with feet together to measure the explosive strength of the lower body.Duration of moderate to vigorous physical activity during physical education classes.A report of the nutritional knowledge and habits regarding the consumption of dairy products, fruits, vegetables, water, legumes, fish and snacks.A report detailing the main types of food purchased at the school kiosk and the amount of money spent.Food offering at the school kiosk: identification of the types of food and their macronutrient contribution.Number of street food carts/stalls that can be found outside the school and their distance in metres from the main school access.

All of the above evaluations will also be conducted after 8 months of intervention (before starting the summer holidays), after 12 months of intervention (return from summer holidays) and after 20 months of intervention (at the end of the second school year).

### Data handling

#### Data acquisition, management and transfer

All of the participants in this study will be identified by their unique national identification number (RUT). The data collected in the field by the field coordinators will be maintained under confidentiality between the field coordinators and the INTA data coordination centre. A unique identification number will be assigned to each participant once they have been registered in the study and their details have been recorded. This unique identification number will be used from that point forward on all relevant documentation. All participant files will be stored and locked in a secured location. Access to these files will be controlled by the field coordinator.

All of the field data collected will be taken to the INTA on a weekly basis, where they will be validated to identify any inconsistencies and rectify errors. Once validated, the data will be entered into the study database.

The INTA data coordination centre will be responsible for registering all of the data files as they are delivered and notifying the field coordinator if any data are missing. The INTA data coordination centre will also be responsible for the safe keeping of the anonymous and encrypted data.

### Data analysis

The data will be validated by the minimum and maximum values. All the statistical analysis will consider the cluster design, in an intention of treating analysis. Additionally, each intervention protocol will be analysed separately to determine the effectiveness of each intervention.

The normality of the data will be assessed by determining the goodness of fit using the Shapiro-Wilk test, while the homogeneity of the variance will be assessed by using the Bartlett and Levene tests. The results from the Shapiro-Wilk test will be used to describe each variable depending on their normality, variables that are normally distributed will be described by the mean ± SD and range of the 95% CI, while variables that do not follow a normal distribution will be described by their percentile distribution. The results will be shown with their respective 95% confidence intervals.

The difference between each group (intervention mode) will be assessed by conducting parametric tests for normally distributed continuous variables (student *t*-test and ANOVA), and non-parametric tests (Wilcoxon, Kruskal-Wallis and Friedman tests) for non-normally distributed continuous variables. The Chi-square test will be conducted for categorical variables (non-continuous). Logistic regression models will also be developed to analyse the probability of change in the result variables for each intervention mode, controlling by age and gender of the participants and considering the impact of the secondary variables. To evaluate the difference between modes of intervention for continuous dependent variables, a multilevel regression analysis with mixed effects will be conducted to make adjustments by co-variables, as these models do consider the experimental design.

STATA 12 (Copyright 1984–2009 StataCorp) and SAS 9.1 (Copyright (c) 2002–2003 by SAS Institute Inc., Cary, NC, USA) will be used to conduct all of the statistical tests and analysis.

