### Outcome measures

#### Healthy Kiosk with nutritional education and optimized physical activity intervention (KSEAN + AFSO)

##### Primary result variable

Nutritional status of the participants after a 2-year intervention.

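### The plan promises cluster-aware analysis throughout, but for the categorical primary outcome and the binary food-intake outcome it names only chi-square and a logistic regression with no school term

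*Protocol article*

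**What the plan says.** All of the following is in the protocol article.

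- Data analysis, general commitment: "All the statistical analysis will consider the cluster design, in an intention of treating analysis".
- Data analysis, methods for differences between modes: t-test and ANOVA or rank tests for continuous variables according to normality, and for the rest "The Chi-square test will be conducted for categorical variables (non-continuous".
- Data analysis, regression: "Logistic regression models will also be developed to analyse the probability of change in the result variables for each intervention mode". Age, gender and the secondary variables are the adjustments listed; school is not among them.
- Data analysis, multilevel model: "To evaluate the difference between modes of intervention for continuous dependent variables, a multilevel regression analysis with mixed effects will be conducted". The reason offered is "as these models do consider the experimental design", and it is said of this model alone.
- Outcome measures, KSEAN+AFSO primary variable: "Nutritional status of the participants after a 2-year intervention". Its operational definition is in classes: "Obese >2 Z of BMI, Overweight >1 Z of BMI", with a normal class below.
- Outcome measures, KSEAN primary variable: "Intake of foods measured as consumed and not consumed".
- Design: 12 schools in three regions, four per region, one to each mode and one to control. That is three schools per arm.

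**The concern.** Whole schools were allocated, so children in one school are not independent observations. The opening commitment recognises this, but the method list does not carry it through. An analyst matching outcome to method by variable type would reach chi-square and logistic regression for nutritional status class and for food intake, and would find no clustered version of either. The multilevel model is out of reach because it is limited to continuous outcomes.

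In their standard form both named methods use the variance of independent children. If schools differ for reasons unrelated to the intervention, that variance is too small and the 5% level is exceeded. Two of the article's primary variables are affected. Food intake is the more exposed, because children in a school share one kiosk and what it sells.

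**Working it through.** **Inputs from the article.** Effect 0.2 SD on BMI z-score, power 0.80, significance 5%, 140 children per school, at least 11 schools and 1,540 children, raised to 12 schools and 1,680 (Determination of sample size). The figure 0.00012 is labelled a coefficient of variance there; I read it as the ICC. I assume two-sided tests. Three schools per arm comes from Design; the sample-size section speaks of four per mode, which does not match. Obesity prevalence of 25.3% in six-year-olds comes from Background.

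**The plan's own figure.** A two-sample comparison of 0.2 SD needs 393 children per arm, so 4 × 393 = 1,572, against 1,540 stated (2.1% apart). The design effect is 1 + (140 − 1) × 0.00012 = 1.017. With it, power is 0.786 at 11 schools and 0.820 at 12 schools (420 children per arm). The stated size is reproduced closely enough, and only with a near-zero ICC.

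**Type I error of an unadjusted test.** With design effect DE = 1 + 139 × ICC:

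- two arms: 2 × [1 − Φ(1.96 / √DE)]
- four arms: P(χ² on 3 df > 7.815 / DE)

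The ICC is on the scale of the outcome tested, taken as a yes/no split such as obese or not. Only the first row uses a value from the article; the others are assumptions.

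| ICC | DE | Two arms | Four arms |
|---|---|---|---|
| 0.00012 | 1.017 | 5.2% | 5.3% |
| 0.001 | 1.139 | 6.6% | 7.6% |
| 0.005 | 1.695 | 13.2% | 20.3% |
| 0.01 | 2.390 | 20.5% | 35.2% |
| 0.02 | 3.780 | 31.3% | 55.9% |

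Example at ICC 0.01: 1.96 / √2.39 = 1.268, and 2 × [1 − Φ(1.268)] = 20.5%.

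A beta-binomial simulation under no effect (40,000 runs, 3 schools × 140 children per arm, prevalence 25.3%) gave 5.1% and 5.1% at ICC 0.00012, 20.3% and 35.2% at 0.01, and 31.4% and 56.0% at 0.02.

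**How small an ICC matters.** Error reaches 10% when DE = (1.960 / 1.645)² = 1.420 for two arms, so ICC = 0.420 / 139 = 0.0030. For four arms, DE = 7.815 / 6.251 = 1.250 and ICC = 0.250 / 139 = 0.0018.

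**Scale of the ICC.** An ICC on the BMI z scale shrinks when the score is cut at 25.3% prevalence, by a factor of about 0.541. BMI z ICCs of 0.01 and 0.02 then give four-arm error of 21.6% and 37.3%. The inflation is smaller but remains.

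**A cluster-valid alternative.** In the same simulations, extended to ICC 0.05, school-level proportions analysed by t-test (3 v 3 schools) or ANOVA (12 schools) held error at 4.8% to 5.1% for every ICC tried.

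**Its power.** For 0.2 SD on BMI z at ICC 0.00012, the noncentrality is 0.2 / √(2 × 1.017 / 420) = 2.87. Power is 0.58 on 4 df (two arms alone), 0.67 on 6 df (12 schools less four arm means and two region terms) and 0.71 on 8 df (four arms pooled, no region terms). The normal approximation gives 0.82.

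**The case against.** The strongest reply is that the opening commitment covers every analysis and makes no exception for categorical outcomes. Logistic regression can carry a random school effect or cluster-robust errors, and chi-square can be design-adjusted. A condensed article may leave that variant to the full protocol or analysis plan. This stands to a point: a reader might infer that the trial has declared an unadjusted, child-level analysis, and the text does not say so. It does not remove the conflict. The article names the tests, and it credits only the continuous-outcome model with respecting the design.

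Three further inferences are tempting and unsupported.

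- **All the obesity outcomes lack a valid test.** They do not. BMI z-score, on which the sample size rests, and body fat are continuous and are assigned the multilevel model. That assignment carries no normality condition, so a Shapiro-Wilk rejection does not cancel it. The Friedman test is loosely placed among between-mode tests, but four measurement times give it a plausible use.
- **Three schools per arm causes the inflation.** It does not. The design effect depends on school size and ICC. Few schools limit the degrees of freedom and power of a valid analysis.
- **Inflation is certain.** It is not. At the protocol's ICC it is negligible, and at 0.001 it is modest.

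**Conclusion.** The concern holds as a conflict between a stated commitment and the methods named for two primary outcomes. Followed as listed, those methods are not valid for school-randomised data.

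The size depends on an ICC that the article does not give for status class or food intake. The value 0.00012 was used for BMI z-score and need not carry over. If it did, error would stay near 5%. Under assumed ICCs of 0.005 to 0.02, two-arm error would be about 13% to 31% and four-arm error about 20% to 56%. These figures assume equal schools of 140, a binary split of the outcome and no adjustment for school. Since an ICC of 0.002 to 0.003 is enough to double the error, the validity of a primary test should not rest on the ICC being almost zero. The point should be corrected before analysis.

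**What to change.** Replace the test-by-variable-type rule with one requirement: every comparison between modes uses a cluster-valid method.

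- **Nutritional status class and food intake:** a mixed logistic or ordinal model with a random school effect.
- **Continuous outcomes:** the multilevel model already planned.
- **All of these:** region as a fixed effect and a small-sample correction that reflects 12 schools. An analysis of school-level summaries is also valid, though it does not estimate the same quantity as a mixed logistic model.
- **Chi-square, t-test, ANOVA and rank tests:** description only.

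The change needs new wording and no new data. P-values will be less favourable, and the plan should state the loss of power. For 0.2 SD on BMI z at ICC 0.00012, comparing three schools with three has power of about 0.58 to 0.71 depending on degrees of freedom (0.67 with region fixed), against the planned 0.80. At higher ICCs it would be lower.

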**Methods:**

Cluster randomized controlled trial. Twelve primary public schools chosen at random over three regions of the country will take part in this study. The sample size consisted of a total of 1,655 children. For each region one school will be selected for each of the three nutritional intervention modes and one school will be selected as the control group. The intervention modes consist of the following:Healthy Kiosk and nutritional education (KSEAN);Optimized physical activity (AFSO);Healthy Kiosk and nutritional education (KSEAN) + optimized physical activity (AFSO);Control group.

The effectiveness of each intervention will be evaluated by determining the nutritional condition of each child by measuring percentage of body fat, BMI and the z-score of the BMI. This study will also identify the eating behaviours, nutritional knowledge and fitness of each child, along with the effective time of moderate activity during physical education classes.

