Physical Activity Intervention: The optimized physical education classes will consider what is already established in the curriculum for the subject physical education and health, with four teaching hours per week, distributed in blocks of 90 min each on different days of the week. Each school selected for this mode of intervention will have a specialized physical education teacher or a teacher with specific training in physical education. Teachers will receive further training to ensure: 1) that the effective class time has a duration of 70 min; 2) that 50% of the effective time consists of activities that demand a moderate to vigorous intensity. Monitoring will be carried out of all of the physical education classes conducted for years 1 to 4, by external physical education teachers that have been previously trained and standardized. They will measure the effective class time and will select children at random to wear the pedometers during the class.

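### The logistic outcome models take in a secondary outcome, percentage of body fat, without limiting it to its baseline value, so the intervention effect they estimate is ambiguous and may be attenuated

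*Protocol article*

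**What the plan says.** The Data analysis section of the protocol article describes three layers of comparison.

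- Group tests without covariates: "The difference between each group (intervention mode) will be assessed by conducting parametric tests for normally distributed continuous variables", with non-parametric and chi-square counterparts.
- Logistic models: "Logistic regression models will also be developed to analyse the probability of change in the result variables for each intervention mode", and these are fitted "controlling by age and gender of the participants and considering the impact of the secondary variables".
- For continuous outcomes, "a multilevel regression analysis with mixed effects will be conducted to make adjustments by co-variables". The covariates of this model are not named.

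Under the heading *Secondary result variable* the article lists one item, "Percentage of body fat". The Abstract (Methods) says that effectiveness will be judged "by measuring percentage of body fat, BMI and the z-score of the BMI", so body fat stands there beside BMI as an effectiveness measure. The primary outcome of the combined arm is nutritional status at two years, defined by cut-points of the BMI z-score. Under *Baseline data collection*, skinfolds are measured at baseline and again at 8, 12 and 20 months.

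Separately, the heading *Control variable* carries "Physical activity intensity measured using a pedometer during the optimized physical activity classes". The description of the physical activity component says that the class monitors "will select children at random to wear the pedometers during the class".

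**The concern.** Percentage of body fat is something the programme is meant to change. A model for BMI-based status that also contains body fat measured after the programme began compares children who ended up equally fat. It therefore asks how far the programme shifted BMI category beyond what body fat already shows. That differs from asking whether the programme worked, and the answer is usually smaller.

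The models affected are not marginal. The primary outcome is categorical and the multilevel model is reserved for continuous outcomes, so the logistic model is the only covariate-adjusted model described that suits the primary outcome. An analyst could follow the sentence using 20-month body fat and report the resulting odds ratio as the effect of the intervention. The trial is sized for a modest standardised effect of 0.2, so even partial attenuation could make a real effect look like little or nothing.

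**Working it through.** The article gives no figure for how much effect such an adjustment would remove, so there is nothing to reproduce. The check is what the rule would do under each reading of when body fat is measured.

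**Inputs**

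- From *Determination of sample size*: intervention effect on BMI z-score, dY = 0.2 SD.
- Assumed, because the documents do not give them: within-arm correlation of follow-up body fat and BMI z-score, rho = 0.3 to 0.85; intervention effect on body fat, dM = 0 to 0.2 SD.
- Assumed for the simulation only: baseline and follow-up body fat correlate 0.85; comparison-arm BMI z-score has mean 0.9 and SD 1; obesity is z above 2, the article's own cut-point; 200,000 independent children per scenario. Leaving out clustering affects precision, not the point made here.

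**Formula (linear scale, both measures in SD units)**

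Adjusted effect = dY − rho × dM.

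Share of effect lost = rho × dM / dY.

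**Follow-up body fat in the model, dY = 0.2**

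| rho | dM | Loss by formula | Simulated linear effect, unadjusted → adjusted | Simulated loss |
|---|---|---|---|---|
| 0.7 | 0 | 0% | −0.197 → −0.201 | none |
| 0.3 | 0.1 | 0.3 × 0.1 / 0.2 = 15% | −0.202 → −0.171 | 15% |
| 0.3 | 0.2 | 30% | −0.201 → −0.141 | 30% |
| 0.5 | 0.2 | 50% | −0.203 → −0.101 | 50% |
| 0.7 | 0.2 | 70% | −0.198 → −0.056 | 72% |
| 0.85 | 0.2 | 85% | −0.208 → −0.033 | 84% |

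More than half the effect is lost only if rho × dM exceeds 0.10 SD. With equal effects on both measures, that means rho above 0.5.

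**Logistic scale (obese or not), dM = 0.2, log odds ratio unadjusted → adjusted for follow-up body fat**

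- rho 0.3: −0.395 → −0.292, a drop of 1 − 0.292/0.395 = 26%
- rho 0.5: −0.393 → −0.223, 43%
- rho 0.7: −0.376 → −0.132, 65%
- rho 0.85: −0.382 → −0.098, 74%

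These drops should be read with care. A log odds ratio moves away from zero when any strong predictor is added: with rho 0.7 and dM = 0 it goes from −0.382 to −0.536. The drops above are net of that movement.

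**Baseline body fat in the model**

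The linear effect stays at about −0.20 in every scenario. The log odds ratio moves slightly away from zero, for example from −0.376 to −0.444 at rho 0.7 and dM 0.2. None of the effect is lost.

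The result therefore turns on which measurement enters the model, and the article does not say.

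**The case against.** The case for leaving the text alone is substantial.

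- *A harmless reading exists.* Skinfolds are taken at baseline, and adjusting for a baseline value removes nothing. The choice of visit may be settled in a fuller protocol or analysis plan that is not shown. This stands as a limit on the claim. However, the article does state a covariate rule, and the variable it admits is headed as a result variable with no restriction to baseline.
- *The verb is loose.* Age and gender are controlled for, while the secondary variables are only considered, which could mean a modifier analysis or a supplementary model. This also stands, although the phrase sits in the clause that lists what the models account for.
- *Body fat is not a second measure of every outcome.* Fitness and food intake are also primary variables, and the overlap with BMI does not apply to them. That is correct; for those outcomes the remaining issue is only that follow-up body fat is measured after allocation.

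A reader might also draw three stronger conclusions, none of which the documents support.

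1. *Most of the effect would be removed.* This needs follow-up values, a high correlation and a body-fat effect about as large as the BMI effect. The article gives none of these, and the computed loss starts at zero.
2. *All outcome models are affected.* The phrase belongs to the logistic models only. The simple group tests carry no such adjustment, and the multilevel model does not mention secondary variables.
3. *The pedometer variable would drop children or whole schools from the model.* No section enters it in a model. The *Control group* section says that controls receive the same evaluations, and *Baseline data collection* lists moderate to vigorous activity in physical education classes among the measurements made at every visit.

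**Conclusion.** The point holds in limited form. The article allows an effectiveness outcome into the logistic models for other outcomes, including the categorical primary outcome, and does not restrict it to its pre-intervention value. If the follow-up value is used, the coefficient is not the total intervention effect and will usually be too small. The loss is 0% with baseline body fat. With follow-up body fat it lies between 0% and about 84% on the linear scale, for a design effect of 0.2 SD and the assumed ranges of rho (0.3 to 0.85) and dM (0 to 0.2 SD). Nothing in the article narrows that range. This is an ambiguity in a stated rule that could do real harm; it does not show that the trial's effect estimate will be wrong.

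**What to change.** In Data analysis, keep the logistic models but remove the secondary variables from them. State that covariates in the effectiveness models are limited to values fixed before the intervention: region, baseline value of the outcome, age and sex. Report follow-up body fat as an outcome in its own right. Label any model that contains follow-up body fat or class activity intensity as an exploratory mediation analysis, separate from the effectiveness results.

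The cost is one sentence in the analysis section. All of the proposed covariates are already collected or fixed by the design, so no new data are needed and the sample size is unaffected.

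### No between-mode analysis names the outcome's own baseline (t1) value or the region block, although both are available by design

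*Protocol article*

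**What the plan says.** Three layers of between-mode analysis appear in the Data analysis section of the protocol article.

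- Two-group and multi-group tests: t-test and ANOVA, their rank-based counterparts, and chi-square for categorical variables. No covariates are attached to these.
- Logistic models for change in the outcomes, "controlling by age and gender of the participants", and also taking account of secondary variables that are not listed there.
- For continuous outcomes, "a multilevel regression analysis with mixed effects will be conducted to make adjustments by co-variables, as these models do consider the experimental design". The covariates are not listed.

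The section also says that all analyses will take account of the clustering and follow intention to treat.

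Elsewhere, Study schedule defines t1 as the point at which "the baseline measurements of all variables will be taken", with further rounds at 8, 12 and 20 months. Design allocates four schools in each of three regions, one to each mode, and Determination of sample size repeats that "each intervention mode must be conducted in each region". Region is therefore the randomisation block.

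**The concern.** The baseline value of an outcome is usually its strongest single predictor, and here it is collected on every child. With only three schools per mode, chance differences at t1 are to be expected. An analysis without the t1 value lets whatever part of them persists to t4 enter the effect estimate, and leaves explainable variance in the error term.

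The only covariates named are weak ones for the outcome on which the trial is sized, because a BMI z-score is already standardised for age and sex. Region fixes the structure of the randomisation, yet no model is said to contain it. What is at stake is the power to detect the 0.2 SD target, and how far the comparison is protected against chance imbalance.

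**Working it through.** **Inputs from Determination of sample size.** The target is a "standard size of the effect of 0.2 on the BMI z-score", "with a power of 0.8, a significance of 5% and an inter-cluster coefficient of variance of 0.00012". I take the last figure as the ICC and the test as two-sided. "140 children per cluster are required along with a minimum of 11 clusters, giving a total of 1540 children", and over three regions "a total of 12 clusters and 1680 subjects are required". Twelve schools over four modes gives three per mode, which I use. The same section also speaks of four clusters per mode, which does not match 12 schools.

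**Inputs assumed.** The correlation r between t1 and 20-month BMI z-score is not in the document, so I show 0.5 to 0.9. An ICC of 0.01 is shown as an alternative.

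**1. The plan's own figure.** n per mode = 2 × (1.960 + 0.842)² / 0.2² = 393 after rounding up. Design effect = 1 + 139 × 0.00012 = 1.0167. 393 × 1.0167 = 399.6 children = 2.85 schools, rounded up to 3. 3 × 4 × 140 = 1680, as stated. No baseline adjustment enters this calculation.

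**2. Unadjusted power, two modes compared.** Variance of the difference = 2 × [ICC + (1 − ICC)/140] / 3, tested on 12 − 4 = 8 school-level df.

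- ICC 0.00012: variance 0.004841, SE 0.0696, 0.2/SE = 2.874. Power is 0.820 by the normal approximation and 0.712 by the noncentral t.
- ICC 0.01: variance 0.01138, SE 0.1067, 0.2/SE = 1.875. Power is 0.379 by the noncentral t.

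Before treatment the same SEs describe chance imbalance in baseline BMI z-score between two modes: 0.070 and 0.107 SD, or 35% and 53% of the 0.2 target.

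**3. Power with t1 and region.** df = 12 − 4 − 2 = 6. In the columns headed (a), the variance is multiplied by 1 − r² at both child and school level. In (b), the baseline explains only within-school variance: 2 × [ICC + (1 − ICC)(1 − r²)/140] / 3. Region is charged its 2 df and credited with no variance reduction.

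| r | 1 − r² | ICC 0.00012 (a) | ICC 0.01 (a) | ICC 0.01 (b) |
|---|---|---|---|---|
| 0.5 | 0.75 | 0.789 | 0.444 | 0.385 |
| 0.6 | 0.64 | 0.847 | 0.503 | 0.401 |
| 0.7 | 0.51 | 0.915 | 0.594 | 0.423 |
| 0.8 | 0.36 | 0.976 | 0.741 | 0.451 |
| 0.9 | 0.19 | >0.999 | 0.944 | 0.488 |
| Unadjusted, 8 df | 1 | 0.712 | 0.379 | 0.379 |

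At the stated ICC, (b) is almost the same as (a), for example 0.787 at r = 0.5.

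**4. Region alone.** At ICC 0.00012, if region explained all variance between schools, the variance would fall by 1.7%, while power on 6 df would be 0.678 against 0.712 on 8 df. At ICC 0.01, with region explaining half of the between-school variance, the variance falls by 29% and power goes from 0.379 to 0.465.

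**The case against.** The strongest reply is that this is an incomplete list in a condensed article. Age and gender belong to the logistic models. The multilevel sentence lists nothing and says these models respect the design, which has region as its block. A reader might infer that the plan excludes the baseline and region. The text does not support that: it does not name them, and a fuller document may. The baseline could also enter through the logistic models of change, or through a mixed model over all four visits.

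That stands, and it limits the point to what is written. It does not remove it. The article does choose analyses and covariates: the t-test, ANOVA and chi-square comparisons use neither term as described, and where covariates are named, the strong one is absent. Modelling a dichotomised change does not replace baseline adjustment of the continuous score.

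Three further objections also stand.

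- Age and gender are not redundant in general. Jump distance, grip strength and food intake are not described as age- or sex-standardised, and in children of 6 to 10 years these covariates are sensible.
- Region is not free precision. At the stated ICC it costs slightly more than it returns.
- Outcome measures defines the primary result as nutritional status in BMI z-score categories. The power figures concern the continuous score used for the sample size, so any remedy must cover both.

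**Conclusion.** The point holds as a recommended improvement. The analyses as described leave out, or leave unnamed, the t1 value and the randomisation block, and a better analysis is available from data already planned.

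At the stated ICC, school-level t-based power is below the planned 0.80 without adjustment (0.712). With both terms it is 0.789 at a correlation of 0.5 and above 0.80 from 0.6 upwards. At an assumed ICC of 0.01 it moves from 0.379 to 0.444–0.944 if school variance shrinks in proportion, but only to 0.385–0.488 if the baseline explains variation within schools alone. These figures assume 140 analysed children per school, SD 1, a two-sided 5% test and no school-level df charged for the child-level t1 value.

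A reader might infer that the plan gives up most of the attainable precision. That requires a correlation above about 0.71 (1 − r² below 0.5) with school variance shrinking too, and the document gives neither. At 0.5 to 0.6 the reduction in variance is 25–36%. The size of the gain is therefore an assumption; its direction held in every scenario computed, even after paying for region.

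**What to change.** Name the between-mode model for each outcome type in Data analysis.

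- **Continuous BMI z-score:** mixed model of the t4 value on mode, t1 value and region (fixed), with a random school effect and tests on school-level degrees of freedom. Age and sex are optional.
- **Body fat, jump and grip:** the same form, each with its own t1 value, plus age and sex.
- **Nutritional-status categories and food intake:** a mixed logistic version with baseline status, mode, region and a random school effect, adding age and sex for intake. The categorical primary outcome stays as defined.
- **t-test, ANOVA, rank and chi-square comparisons:** keep as descriptive only.

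No new data are needed. The cost is wording and a fall from 8 to 6 school-level df, which at the stated ICC is a small loss attributable to region and is outweighed by the t1 adjustment over the correlations shown. If comparisons by mode have already been run, report this as a dated change alongside the analysis as written.
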